# Early screening for *Chlamydia trachomatis* in young women for primary prevention of pelvic inflammatory disease (i-Predict): study protocol for a randomised controlled trial

**DOI:** 10.1186/s13063-017-2211-1

**Published:** 2017-11-13

**Keywords:** *Chlamydia trachomatis*, Infection, Clearance, Reinfection, Screening, Pelvic inflammatory disease, Prevention, Students, Immunogenetics, Natural course of infection

## Abstract

**Background:**

Genital infection with *Chlamydia trachomatis* (Ct) is the most common bacterial sexually transmitted infection, especially among young women. Mostly asymptomatic, it can lead, if untreated, to pelvic inflammatory disease (PID), tubal factor infertility and ectopic pregnancy. Recent data suggest that Ct infections are not controlled in France and in Europe. The effectiveness of a systematic strategy for Ct screening in under-25 women remains controversial. The main objective of the i-Predict trial (Prevention of Diseases Induced by *Chlamydia trachomatis*) is to determine whether early screening and treatment of 18- to-24-year-old women for genital Ct infection reduces the incidence of PID over 24 months.

**Methods/design:**

This is a randomised prevention trial including 4000 eighteen- to twenty-four-year-old sexually active female students enrolled at five universities. The participants will provide a self-collected vaginal swab sample and fill in an electronic questionnaire at baseline and at 6, 12 and 18 months after recruitment. Vaginal swabs in the intervention arm will be analysed immediately for Ct positivity, and participants will be referred for treatment if they have a positive test result. Vaginal swabs from the control arm will be analysed at the end of the study. All visits to general practitioners, gynaecologists or gynaecology emergency departments for pelvic pain or other gynaecological symptoms will be recorded to evaluate the incidence of PID, and all participants will attend a final visit in a hospital gynaecology department. The primary endpoint measure will be the incidence of PID over 24 months. The outcome status (confirmed, probable or no PID) will be assessed by two independent experts blinded to group assignment and Ct status.

**Discussion:**

This trial is expected to largely contribute to the development of recommendations for Ct screening in young women in France to prevent PID and related complications. It is part of a comprehensive approach to gathering data to facilitate decision-making regarding optimal strategies for Ct infection control. The control group of this randomised trial, following current recommendations, will allow better documentation of the natural history of Ct infection, a prerequisite to evaluating the impact of Ct screening. Characterisation of host immunogenetics will also allow identification of women at risk for complications.

**Trial registration:**

ClinicalTrials.gov, NCT02904811. Registered on September 14, 2016.

World Health Organisation International Clinical Trials Registry, NCT02904811.

AOM, 15-0063 and P150950. Registered on September 26, 2016. A completed Standard Protocol Items : Recommendations for International Trials (SPIRIT) Checklist is available in additional file 1.

**Electronic supplementary material:**

The online version of this article (doi:10.1186/s13063-017-2211-1) contains supplementary material, which is available to authorized users.

## Background

### Epidemiology of genital infections with *Chlamydia trachomatis* and further complications

Genital infection with *Chlamydia trachomatis* (Ct) is the most common bacterial sexually transmitted infection (STI) [1]. Ct affects predominantly young women (18–24 year old), with an estimated prevalence of 3.6% in 2005 in France [2]. The number of Ct diagnoses has increased over the past 10 years in France as well as in other European countries. Interestingly, in 2012, the proportion of positive tests reached 8.3% of 18- to 24-year-old women participating in a web-based study promoting home screening in France [3]. Although these trends may be partly explained by an increase in screening activities, particularly targeting at-risk populations, they may reflect a true increase in incidence.

Because the majority (~70–80%) of lower genital tract Ct infections in women remains asymptomatic [4], patients may not seek testing for care. If untreated, genital chlamydial infection can ascend to the upper genital tract, leading to serious complications [5] such as pelvic inflammatory disease (PID), tubal factor infertility [6] and ectopic pregnancy [7, 8].

### Prevention strategies in France and in other European countries

Early diagnosis and antibiotic treatments have been considered a major strategy for prevention of complications and further transmission of Ct infection. In France, the national chlamydia control strategy includes sexual health education, awareness campaigns, promotion of condoms and at-risk population screening. Systematic (routine) screening in young sexually active women has not been implemented. Instead, opportunistic screening for Ct infection is offered to women younger than 25 years old if they visit STI clinics, reproductive health services or abortion centres [9]. A systematic screening programme was introduced throughout England in 2007 for sexually active men and women younger than 25 years old attending various clinical and non-clinical settings (e.g., universities and sporting events), but the effectiveness of systematic screening to prevent PID remains controversial.

### Gaps in knowledge

To date, there have been three published randomised trials in which researchers investigated whether early screening and treatment of young females would reduce the incidence of PID over a 12-month period [10–12]. The most recent and methodologically sound study, the prevention of pelvic infection (POPI) trial conducted in England, yielded inconclusive results. Moreover, most PID cases occurred in women who had a negative test result for Ct at baseline, raising the question of the optimal frequency of testing [12].

Key characteristics of Ct infection natural history (i.e., rate and timing of progression of lower genital tract infection to PID) are not sufficiently documented. Yet, accurate estimates of these characteristics are needed to better anticipate the benefit of early and systematic screening for infection. Further, the average duration of Ct infection in the absence of treatment is not well established and could possibly be 1 year or longer [13]. Finally, reinfection is common following therapy (10–20% patients within 12 months) [14, 15], thus raising questions about host immune response and the relevance of and time to retesting.

Inter-individual variations in host immune response may explain why some women develop complications such as PID after Ct infections and others do not. Among various genetic markers, single-nucleotide polymorphisms (SNPs) have been shown to be related to the development of late complications of Ct infections in women [16, 17]. This approach could be relevant to identifying women at risk for PID and tubal pathology and adapting treatment and follow-up for these women. In summary, there is a need to evaluate the efficacy of early screening for prevention of PID and to better understand the natural history of Ct infection and progression to PID in order to develop efficient screening programmes in France.

### Main objective

The main objective of this study is to determine whether early screening and treatment for genital Ct in young women (<25 years of age) in France reduces the cumulative incidence of PID over 24 months.

### Secondary objectives

The following are secondary objectives of this study:To determine the baseline prevalence and the incidence of Ct infectionTo improve knowledge of the natural history of Ct infection in young women, including rate and timing of progression to PID, as well as the incidence of Ct reinfectionTo investigate the relationship between host immunogenetics (SNPs), Ct clearance, persistence, and development of late complications (PID) as an explanatory factor for inter-individual heterogeneity in Ct susceptibility and infection progression.

To reach these objectives, the i-Predict trial (Prevention of Diseases Induced by *Chlamydia trachomatis*) leverages the existing i-Share cohort (Internet-based Students HeAlth Research Enterprise), the largest French prospective cohort, aiming at recruiting 30,000 students followed for at least 10 years with yearly assessments of their health. Participants in i-Share are asked to complete baseline and follow-up web-based questionnaires through a dedicated study website (www.i-share.fr). The objective of i-Share is to evaluate the frequency of diseases affecting students and related risk factors. It is also meant to serve as a platform to nest interventional studies on specific topics related to students’ health.

## Methods/design

### Design/setting

This is a randomised controlled trial spanning 24 months. It is a single-blinded study nested within the i-Share cohort study (Fig. 1).

**Fig. 1 Fig1:**
[figure not shown]
Design of the i-Predict trial according to the SPIRIT checklist. *Ct Chlamydia trachomatis*

### Participants

Inclusion criteriaFemale student registered at a French university participating in the i-Share cohortAged 18 to 24 yearsSexually activeSigned written informed consentCovered by the French National Health Insurance programme
Non-inclusion criteriaReported pregnancy

### Intervention

#### Experimental group

Vaginal samples from the intervention group (collected at months 0, 6, 12 and 18) will be tested immediately for Ct infection. Participants with positive results for Ct will be asked to attend a visit with their general practitioner or gynaecologist or at the nearest STI clinic to be examined and treated, and they will be informed of the need for their partner to be treated (‘patient referral’ is acceptable in this French setting).

#### Control group

The control group will perform self-taken vaginal samples at the same frequency as the intervention group, but testing will be deferred until the end of the 18-month study period to allow study of the natural course of Ct infection in the absence of testing and treatment. Results for Ct will be made available to the gynaecologist at the final visit for adequate care. During the whole study, participants will follow current screening guidelines (i.e., screening in case of symptoms or if they attend STI clinics).

### Blinding

Participants will be blinded to their group assignment until the end of the trial except for those who will be informed of a positive result in the intervention group. Two independent experts will review symptoms data from medical records and symptoms collected during the final visit to classify outcome status (confirmed, probable or no PID). These medical experts will be blinded to group assignments and Ct status.

### Recruitment, randomisation, follow-up and data collection

i-Predict is nested within the i-Share cohort; therefore, information provided to the students in the i-Predict trial will be available on the i-Share website, redirecting volunteers to the university health service (UHS) to be included. Participants in i-Share who fit the inclusion criteria for i-Predict (age and sex) will be solicited via emails to participate. Participants can also be informed about i-Predict and asked to participate at each UHS of the five participating universities without knowledge of the existence of the i-Share cohort or solicitation through the i-Share cohort. In this case, they will also be enrolled in the i-Share cohort just before the i-Predict initial visit. A schedule of enrolment, interventions and assessments of the i-Predict trial is shown in Fig. 2.

**Fig. 2 Fig2:**
[figure not shown]
Schedule of enrolment, interventions and assessments of the i-Predict trial. *Ct Chlamydia trachomatis*, *PID* Pelvic inflammatory disease

#### Initial visit

Female students will be enrolled at each UHS for a period of 2 years. They may already be enrolled, or they may be new participants in the i-Share cohort (i.e., enrolled during the visit at which they will be offered to participate in both the i-Share cohort and the i-Predict trial).

Eligible participants will be approached by the physician investigator, provided information on the study and asked to sign an informed consent form if they agree to participate. They will be randomly allocated to the intervention or control group.

Participants will complete a baseline electronic self-administered questionnaire on their sexual and gynaecological history, use of hormonal contraception and condoms, and possible symptoms of infection. They will also provide a self-collected vaginal sample (month 0) on site.

Additionally, the following sociodemographic and medical data from the i-Share baseline questionnaire will be retrieved at baseline: type of training; year of registration; dwelling place; medical history; medical appointments; medication consumption; eating habits; well-being; and tobacco, alcohol and drug use.

#### Randomisation

Block randomisation, stratified by participating university (Versailles Saint-Quentin-en-Yvelines, Bordeaux, Nice Sofia-Antipolis, Paris Sorbonne Universités, and Sorbonne Paris Cité), will be used to assign eligible participants who have provided informed consent to each group (1:1 ratio), resulting in one intervention group and one control group. Site-specific randomisation will be performed in the UHS of each of the five participating universities by the principal investigator at each site on the Cleanweb® electronic platform as soon as student recruitment is registered during the initial visit. Group assignment is generated at the same time as the participant’s study identification number; only principal investigators at each site and dedicated staff from the Centre National de Référence (French National Reference Centre for Chlamydial Infections) (CNR) have access to group assignment.

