#### Investigating centres

UHS and GED are involved in the recruitment, inclusion and follow-up of participants. They collect informed consent from the participants and implement randomisation. They are responsible for notifying the sponsor’s vigilance division of any adverse event by filling in the adverse event section of the electronic case report form (Cleanweb® electronic platform).

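### Site principal investigators randomise in university-stratified blocks and keep sight of every woman's arm while their sites recruit and follow up: an avoidable risk, not a shown bias

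*Protocol article*

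**What the plan says.** Under Randomisation, the article describes "Block randomisation, stratified by participating university", 1:1, among women who have consented. On who does it: "Site-specific randomisation will be performed in the UHS of each of the five participating universities by the principal investigator at each site". On timing: "Group assignment is generated at the same time as the participant’s study identification number", once recruitment has been registered at the initial visit. On access, it names "only principal investigators at each site and dedicated staff from the Centre National de Référence".

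Under Investigating centres, the same sites have a wider role: "UHS and GED are involved in the recruitment, inclusion and follow-up of participants". Under Follow-up, forms from outside physicians arrive at the university health service (UHS), and a clinical research assistant enters them. A woman who reports pelvic pain online is contacted within 24–48 h and encouraged to attend a gynaecology emergency department (GED). Reminders go out by email or phone.

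Under Initial visit, the sentence "They will be randomly allocated to the intervention or control group" comes before the baseline questionnaire and the on-site swab. Blinding is stated for participants (unless told of a positive result) and for the two experts who classify PID. It is not stated for site staff.

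**The concern.** The person who generates each assignment also sees all earlier ones at that university. In permuted blocks, earlier assignments carry information about the next. If that person also has a say in who is approached or when, the next allocation is not fully protected.

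The primary endpoint depends on a woman with pain being seen and documented. The blinded experts can classify only what reaches them. A site investigator who knows the arm could, without intending it, pursue pain reports or missing forms more keenly in one arm, or remind controls more often that they may be tested elsewhere. The first would distort the relative risk (RR) and the second would dilute the contrast. The analysis could separate neither from a true effect.

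The article gives no task for which the site needs the arm of controls or of test-negative women. The reference laboratory does need the arm, because it tests intervention swabs on arrival and stores control swabs.

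**Working it through.** The plan states no figure on this point, so there is none to reproduce. The check sets the passages side by side and then gives two illustrations of scale.

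**What the text settles**

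| Step | Who | Knows the arm? |
|---|---|---|
| Approach and consent | Physician investigator | Not stated whether this is the principal investigator |
| Randomisation | Site principal investigator | Yes, once generated, and afterwards |
| Swab handling | Reference laboratory staff | Yes, needed |
| Data entry at the UHS | Clinical research assistant | Not on the access list |
| Contact after a pain report | Not named | Not stated |
| PID classification | Two experts | Blinded |

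**Illustration 1: predicting the next assignment.** Assumptions: a fixed block size known to the guesser, all earlier assignments at the site known, and a guess always for the arm with more places left. For a block of 4, by position:
- first: 1/2
- second: 2/3
- third: (1/3 × 1) + (2/3 × 1/2) = 2/3
- fourth: 1

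The sum is 2.83, and 2.83/4 = 71%. In general, for block size 2b, expected correct guesses are b + 2^(2b−1)/C(2b,b) − 1/2. With b = 3 this is 3 + 32/20 − 0.5 = 4.10, and 4.10/6 = 68%. Without knowledge of past assignments the figure is 50%.

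The share of women whose arm is certain beforehand is 1/(b+1): 33% for blocks of 4 and 25% for blocks of 6. For blocks of 8 and 10 the best guess is right 67% and 65% of the time.

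**Illustration 2: sensitivity of the endpoint.** Inputs from Sample size: 2000 per arm less 10% attrition = 1800, RR 0.54, one-sided 5%, 80% power. The control risk that gives this power under the usual two-proportion formula is about 2.45%:
- control cases: 1800 × 0.0245 ≈ 44
- intervention cases: 0.54 × 44 ≈ 24

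Suppose 10% of cases in one arm went uncaptured (an assumption; the article gives no such rate). That is about 2 cases in the intervention arm or 4 in the control arm. The RR of 0.54 would read 0.54 × 0.9 = 0.49 or 0.54 / 0.9 = 0.60.

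With no true effect, the same 10% loss in the intervention arm gives an apparent RR of 0.90. The risks are 0.0245 and 0.0221, the standard error is about 0.0050, and z = 0.0025/0.0050 ≈ 0.49. The chance of exceeding 1.645 is then about 12% instead of 5%. For losses of 5% and 20% it is about 8% and 26%.

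**The case against.** A reader might infer that recruitment and PID ascertainment are in fact biased, or that allocation is not concealed. The text does not support either, and the case against those readings is strong.

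- **Concealment of the current assignment holds.** It is generated electronically after consent and registration.
- **The predictability figures rest on an assumption.** Block size and any variation in it are not in the article, which may properly leave them to the full protocol. Varying block sizes would lower the figures.
- **The principal investigator is not the whole site.** Research assistants who enter the data are off the access list, and nothing gives the principal investigator a part in assessing PID.
- **Procedures are the same in both arms.** The pain questionnaire, the contact that follows it and the final visit apply to everyone, and the article mentions automatic electronic reminders.
- **The trial is declared single-blind,** so the access contradicts nothing.
- **Baseline data are self-reported and self-collected by blinded women,** so moving them before allocation gains little.
- **Referral of positive results is a plausible reason for some site access.**

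All of this stands against a claim of demonstrated bias. It does not justify the access as written. Referral needs knowledge of positive intervention-arm women only, not of every woman. The person who makes pain contacts is not named, and blinding is not stated for that role. The final visit may not reveal an episode that has already resolved. The access is a written rule, so this is not a complaint about detail left to another document.

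**Conclusion.** The point holds as an avoidable design risk. The site principal investigator randomises in university-stratified blocks and keeps sight of every assignment, while the same site recruits, follows up and receives PID forms. The article gives no stated need for that breadth of access.

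Two risks remain: prediction of the next assignment, and arm-dependent contacts, reminders or advice on outside testing. The size of the first depends on the block scheme and on whether the principal investigator also approaches women, neither of which is given. The 71% and 68% apply only to known fixed blocks of 4 and 6. The size of the second is unknown. The 10% loss in the working shows how few cases would matter and is not an estimate. The direction could be either way.

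It is worth correcting because the remedy is cheap, but it does not by itself call the trial's result into question.

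**What to change.** 1. On the electronic platform, restrict group assignment to the dedicated reference laboratory staff.
2. At randomisation, show the site only the study number.
3. Disclose to the site only those women with a positive intervention-arm result that must be acted on, so that the protocol's existing referral route is kept.
4. Complete the baseline questionnaire and swab before the allocation is generated, and say so under Initial visit.
5. State that staff who make pelvic-pain contacts and reminders are blinded to arm.

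This costs a permission setting on a platform already in use and a small amendment. The downside is that the laboratory must route positive results, and the site remains unblinded for those women, so the risk is reduced and not removed. Enrolment has begun, so assignments already seen cannot be hidden again. The change protects later recruitment and the follow-up of women randomised after it.

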#### Follow-up

All participants will self-collect vaginal samples in the privacy of their home at months 6, 12 and 18. A kit including detailed self-sampling instructions will be mailed to them a few days prior to each due date. Participants will mail the sample back to the CNR and complete an electronic self-administered questionnaire about their number of sexual partners, condom use, symptoms such as abnormal vaginal discharge or pelvic pain, additional testing since their previous sample, medical visits and antibiotic use (for Ct or other infections).

Participants with a positive test result for Ct at baseline or months 6, 12 or 18 in the intervention group will be referred to their physician or the nearest STI clinic for treatment. Of note, current recommendations for uncomplicated infections include a single-dose therapy of azithromycin (1 g) or a 7-day course of doxycycline [18].

The physician collecting clinical data upon examination will fill out a specific form, handed out by the participant together with a prepaid envelope, on clinical findings, as well as treatment initiated, results of additional tests or ultrasound (if any), and information regarding whether a partner was treated (if available). These data will be received at the UHS and entered by a trained clinical research assistant on the Cleanweb® platform.

At any moment during follow-up, all participants will be asked to complete a short, self-administered questionnaire online each time they feel unusual lower abdominal pain. A contact will be made with the participant 24–48 h after completion of this short pelvic pain questionnaire to encourage the participant to visit the closest participating gynaecology emergency department (GED), where they will be evaluated for PID according to current national recommendations by the Collège National des Gynécologues et Obstétriciens Français [19]. Data from these visits to the GED will be made available to the trained clinical research assistant, who will collect them using a standardised clinical research form and enter the clinical data on the Cleanweb® platform.

Unscheduled visits to general practitioners and gynaecologists for gynaecologic symptoms are expected to occur, during which participants may receive a diagnosis of PID. Clinical data from these consultations will be collected using a specific form filled out by the physician and handed out by the participant together with a prepaid envelope (clinical examination, treatments, results of additional tests or ultrasound if any). This form will be received at the UHS, and data will be entered on the Cleanweb® platform by a trained clinical research assistant. During the follow-up phase, participants will be reminded by email or by phone to collect the swab and fill out their questionnaires.

